### Statistical evaluation and sample size

The hypothesis of this phase III study is that the use of EN will improve the fistula closure rate at 30 days after randomization. According to Klek et al. [16], the 30-day fistula closure rate is expected to be 35% in the TPN group and 55% in the EN group. According to Rutegård et al. [27], we expect 10% mortality within 30 days. Considering a 35% fistula closure rate in the TPN group and an expected 55% rate in the EN group (absolute difference of 20%, relative risk 1.57), a two-sided test, a type I error of 0.05, a 90% power, an allocation rate of 2:1 for the EN group and the TPN group, respectively, and taking into account 30-day mortality of 10%, 214 patients are needed in the EN group and 107 in the TPN group, leading to a total number of 321 patients to be recruited.

The intention-to-treat (ITT) population will comprise all randomized patients, whether or not they satisfy the eligibility criteria and irrespective of the study treatment actually received. Unless otherwise indicated, all efficacy and safety analyses (including the primary outcome) will be conducted on the ITT population.

The per-protocol (PP) population will consist of all ITT patients who complied with the protocol requirements. Compliance with protocol requirements will be addressed through the review of protocol deviations/violations at the time of a blind data review meeting, just prior to database lock. Any significant issues may warrant patient exclusion of all or part of their assessment data. The PP population will be applied only for the primary outcome and will be considered as a secondary analysis. For example, if an EN subject was intolerant for 48 h, and then switched to TPN for support, they will be analyzed in the EN group in the ITT analysis and the TPN group in the PP analyses.

No interim analysis is planned.

Statistical analyses will be independently performed by the Biostatistics Department of the University of Lille under the responsibility of AD. Data will be analyzed using SAS software (SAS Institute Inc., Cary, NC, USA) and all statistical tests will be performed with a two-sided alpha risk of 0.05. A detailed statistical analysis plan will be written and finalized prior to the database lock. The data analysts will be blinded to the treatment arm. Any deviation from the protocol-specified analysis will be documented within a protocol amendment or statistical analysis plan, as appropriate, and described within the clinical study report.

Patient accountability will be summarized by treatment group and overall for all randomized patients. In addition, patient accountability information for screen-failure patients will be collected and reported. The number of patients randomized will be summarized along with the number of patients within each patient population. In addition, the number of patients completing/not completing the study will be presented along with the primary reason for withdrawal from the study.

Deviations that warrant patient exclusion from the PP population will be determined just prior to database lock and documented within the relevant patient listing.

Some subgroup analyses, considered as exploratory, will be performed according to some well-known factors linked to the primary outcomes and considered in the randomization per minimization technique: 1) type of fistula (high- versus low-output fistula where high-output fistula is defined as effluent greater than 200 ml/24 h); 2) malignant/nonmalignant disease; and 3) somatostatin analog use or not.

Baseline characteristics will be described for each arm for the ITT population. Quantitative variables will be expressed as mean (standard deviation), median (interquartile range) and range. Qualitative variables will be expressed as frequencies and percentages. Normality of distributions will be assessed graphically and using the Shapiro–Wilk test.

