### Treatment methods

Each nutritional support will be planned to provide a similar amount of calories and proteins. According to the French guidelines on perioperative nutrition [23] the amount of calories will be 30–35 kcal/kg/day including proteins. The protein or amino acid intake will represent 18–20% of caloric intake: 1.35–1.5 g/kg/day (i.e., nitrogen at 0.21–0.24 g/kg/day).

EN or TPN will start in the first 72 h following randomization with the need for tube or catheter placement (if not already placed and according to randomization arm) in the meantime.

EN can be delivered through a jejunostomy or a nasojejunal tube. A polymeric hypercaloric hyperprotidic product without immunonutrients will be chosen. The nutritional product will be the one usually used in each center. EN will be started slowly (20 ml/h) with a progressive increase in the infusion rate every day according to the tolerance of the patient. The expected infusion rate to cover nutritional needs should be obtained in a week. If the tolerance of EN does not allow the energy and protein requirements to be met at the end of the first week it will be necessary to start a complementary parenteral nutrition to make up the nutritional requirements. EN will be infused at a continuous rate via an enteral pump. In the case of obstruction or failing of the enteral tube, a feeding tube should be replaced immediately with the agreement of the surgeon. If it is impossible to replace an enteral tube, parenteral nutrition should be started on the same day.

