### Medico-economic analysis

Considering the clinical design, a full economic evaluation will be performed taking into account both benefits and costs. The analysis will be conducted in concordance with Haute Autorité de Santé guidelines [28]. Cost-effectiveness analysis will be performed according to the ITT principle and from a societal perspective. A PP complementary analysis is planned as many patients are expected to switch from TPN to EN. The following costs will be considered in the economic analysis: 1) hospitalization (inpatient and home settings); 2) nutritional products; and 3) management of early (before 30 days after randomization) and late (over 30 days after randomization) complications occurring during follow-up.

The costs of hospitalization (inpatient) will be computed using the French hospital production costs study (Echelle Nationale des Couts à la Methodologie Commune Medecine Chirurgie Obstetrique). The average cost will be adjusted to the length of stay (secondary end point) and the number of days in intensive care units, which are known to be the main cost drivers. Home hospitalizations will be valued by reference to the French home hospitalization production costs study (Echelle nationale des Couts-Hospitalisation à Domicile). All hospitalizations will be recorded in the electronic case report form (gathering data on the hospital to which the patient was admitted, their main diagnosis, the date of admission and the date of discharge) at each scheduled clinical examination. Information on diagnosis-related groups (Groupe Homogène de Malades; inpatient setting) or management-related groups (Groupe Homogène de Prise en Charge; home care setting) will be requested at the end of the study by the study coordinator from hospitals to which patients were admitted. Nutritional products will be valued at their current price.

Quality-adjusted life years will be computed using the French value set by a linear interpolation between dates of measurement (inclusion and days 30, 60, 90 and 180) [29]. Considering follow-up, costs and quality-adjusted life years will not be discounted.

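### The per-protocol example counts an EN patient who switched as a TPN patient, which contradicts the per-protocol definition and breaks the randomised comparison in that secondary analysis

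*Protocol article*

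**What the plan says.** All references are to the protocol article.

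- **Definition** (Statistical evaluation and sample size): "The per-protocol (PP) population will consist of all ITT patients who complied with the protocol requirements". Compliance is judged at a blind data review just before database lock. Significant problems may lead to exclusion of a patient or of part of the data. The same section later speaks again of deviations that exclude a patient from the PP set. Nothing in the definition moves a patient to the other arm.
- **Worked example** (same paragraph as the definition): an EN patient is intolerant for 48 h and switches to TPN. For such patients, "they will be analyzed in the EN group in the ITT analysis and the TPN group in the PP analyses".
- **Role**: ITT is the population for the primary outcome. On PP, the section says "The PP population will be applied only for the primary outcome" and calls it a secondary analysis.
- **Second use** (Medico-economic analysis): "A PP complementary analysis is planned as many patients are expected to switch from TPN to EN".
- **Parenteral nutrition within the EN arm** (Treatment methods): "If it is impossible to replace an enteral tube, parenteral nutrition should be started on the same day". The section also provides for complementary parenteral nutrition when EN does not meet requirements after the first week. Protocol overview lists a switch to TPN among the responses to a reportable interruption of allocated treatment.

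**The concern.** The definition and the example cannot both be followed. Under the definition, a patient who switched is either compliant and stays in EN, or non-compliant and is left out. The example does neither: it keeps the patient and changes the arm.

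The change of arm depends on something seen only after randomisation and only under EN. The Background section describes how EN might raise output by reflux or enzyme activation and so lower the chance of closure. If intolerance marks such patients, the example removes poor outcomes from EN and credits them to TPN. The 2:1 allocation magnifies this, because each 10% of EN patients who switch adds about 21 patients (0.10 × 214 = 21.4) to a comparator of 107.

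At stake is the only PP analysis of the primary endpoint in an open-label trial. Readers will use it to judge whether the ITT result is robust. If the economic PP analysis uses the same rule, it has the same flaw.

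**Working it through.** **Inputs from the article.** "Considering a 35% fistula closure rate in the TPN group and an expected 55% rate in the EN group"; "a type I error of 0.05, a 90% power"; "all statistical tests will be performed with a two-sided alpha risk of 0.05"; 2:1 allocation; 10% 30-day mortality; 214 EN and 107 TPN.

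**Step 1: the plan's own figure.** With k = 2 and p̄ = (0.35 + 2 × 0.55)/3 = 0.4833,

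n(TPN) = [1.960 √(1.5 × p̄(1 − p̄)) + 1.2816 √(0.35 × 0.65 + 0.55 × 0.45/2)]² / 0.20² = (1.1996 + 0.7595)² / 0.04 = 95.95, rounded up to 96.

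Allowing for 10% mortality, 96/0.90 = 106.7, rounded up to 107 TPN. Hence 214 EN and 321 in total, exactly as stated. The sample size is not in question.

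**Step 2: model of the example under no effect.** Both arms close at rate p. A share s of EN patients switches and closes at rate q. Neither s nor q is in the article, so both are assumptions. Then

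- EN patients who stay close at (p − s·q)/(1 − s); this is the EN group after reassignment.
- The TPN group after reassignment closes at (107·p + 214·s·q)/(107 + 214·s).

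Example with p = 0.40, s = 0.15, q = 0.20: EN = (0.40 − 0.03)/0.85 = 43.5%. TPN = (42.8 + 6.42)/(107 + 32.1) = 49.22/139.1 = 35.4%. The false difference is 8.1 points.

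**Step 3: range for one-way EN-to-TPN switching, with switchers closing at half the average rate.** Rejection is for the two-sided pooled two-proportion z-test at 0.05, by simulation.

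| p | q | s | Moved to TPN: difference, rejection | Excluded: difference, rejection |
|---|---|---|---|---|
| 35% | 17.5% | 10% | +4.9 points, 14% | +1.9 points, 6% |
| 35% | 17.5% | 20% | +9.4 points, 42% | +4.4 points, 11% |
| 40% | 20% | 10% | +5.6 points, 17% | +2.2 points, 7% |
| 40% | 20% | 15% | +8.1 points, 31% | +3.5 points, 9% |
| 40% | 20% | 20% | +10.7 points, 50% | +5.0 points, 13% |

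Kept in EN (ITT), the difference is 0 and rejection about 5% in every row. In each row the reassignment gives at least twice the bias of plain exclusion.

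**Step 4: sensitivity to the prognosis of switchers (p = 35%, s = 10% to 30%).**

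- q = 35%, the average: no bias.
- q = 25%: +2.8 to +8.0 points.
- q = 10%: +6.9 to +20.1 points. The upper end is as large as the whole planned effect, but needs 30% switching.
- q = 45%: −2.8 to −8.0 points; the sign reverses.

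**Step 5: switching in both directions.** The example covers only EN to TPN. Assume that TPN-to-EN switchers are moved by the same logic.

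- p = 40%, 15% of EN and 30% of TPN switching, all switchers closing at 20%: 32.1 patients move each way. EN = (181.9 × 0.4353 + 6.42)/214 = 40.0%. TPN = (36.38 + 6.42)/107 = 40.0%. The bias cancels.
- p = 35%, 10% of EN and 30% of TPN switching, all closing at 17.5%: EN 34.2%, TPN 36.9%, difference −2.8 points.
- p = 35%, 20% switching in each arm, all closing at 17.5%: +4.9 points, because of the 2:1 allocation.
- p = 35%, 10% of EN switching (closing at 17.5%) and 30% of TPN switching (closing at 45%): +10.3 points.

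**The case against.** The strongest reply has four parts.

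1. **Direction.** A reader might infer that the rule makes EN look better whatever the truth. The article does not support that: it gives no intolerance rate and no closure rate for switchers. The one flow whose size it comments on is TPN to EN, and Step 5 shows that this flow can cancel or reverse the bias. This part stands. The bias is real in kind, but its sign and size are unknown.
2. **Compliance.** A reader might infer that the patient in the example followed the protocol and so must stay in EN. Treatment methods does not establish this. The same-day start of parenteral nutrition concerns a tube that cannot be replaced. For poor tolerance, the section describes complementary parenteral nutrition after the first week, not a full switch after 48 h. This part stands too, but it does not rescue the example: whether compliant or excluded, the patient does not become a TPN patient.
3. **Costs.** A reader might infer that the costs of failed EN will be charged to TPN. Medico-economic analysis does not say that the reassignment rule applies there, and its stated reason for a PP analysis is the opposite flow. Only the conflict over where PP is used is established.
4. **Weight.** PP is secondary, the primary analysis is ITT, and no decision rule or sample size depends on PP. Compliance review is already blind, and so are the data analysts. This limits the severity, but blinding does not remove the bias, because the rule itself causes it.

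**Conclusion.** Wrong as written, and it should be fixed. The example contradicts the definition in its own paragraph and turns the secondary PP analysis of 30-day closure into a non-randomised, as-treated comparison. With no true effect, one-way switching of 10% to 20% of EN patients who close at half an average rate of 35% to 40% (all assumed, except that 35% is the planned TPN rate) gives EN a false advantage of about 5 to 11 points, with 14% to 50% rejection instead of 5%. The bias is zero if switchers are of average prognosis, and of either sign once switching in both directions is allowed. An unpredictable sign is itself a reason not to use the rule.

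The point does not reach the ITT primary analysis or the sample size, and it does not show that the trial's main conclusion would be biased. Separately, the two sections disagree on whether PP is confined to the primary outcome.

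**What to change.** In Statistical evaluation and sample size:

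- Delete the worked example.
- State that PP patients are analysed in the arm to which they were randomised, after exclusion of those with major deviations, as judged at the blind review already planned.
- State whether parenteral nutrition started under Treatment methods counts as a deviation for PP, and that it never changes the arm.

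If an analysis by nutrition actually received is wanted, either label it as-treated and exploratory, or use an estimate that keeps the randomised groups, such as a complier-average effect. Exclusion alone still leaves some bias (Step 3), so PP should remain supportive only.

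Make this section and Medico-economic analysis agree on where PP is used, and apply the as-randomised rule in both.

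The cost is wording in the protocol and the analysis plan, to be settled before database lock. There is no change to sample size, conduct or data collection. The PP result may be less favourable to one arm than under the reassignment.

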### Medico-economic analysis

Considering the clinical design, a full economic evaluation will be performed taking into account both benefits and costs. The analysis will be conducted in concordance with Haute Autorité de Santé guidelines [28]. Cost-effectiveness analysis will be performed according to the ITT principle and from a societal perspective. A PP complementary analysis is planned as many patients are expected to switch from TPN to EN. The following costs will be considered in the economic analysis: 1) hospitalization (inpatient and home settings); 2) nutritional products; and 3) management of early (before 30 days after randomization) and late (over 30 days after randomization) complications occurring during follow-up.

The costs of hospitalization (inpatient) will be computed using the French hospital production costs study (Echelle Nationale des Couts à la Methodologie Commune Medecine Chirurgie Obstetrique). The average cost will be adjusted to the length of stay (secondary end point) and the number of days in intensive care units, which are known to be the main cost drivers. Home hospitalizations will be valued by reference to the French home hospitalization production costs study (Echelle nationale des Couts-Hospitalisation à Domicile). All hospitalizations will be recorded in the electronic case report form (gathering data on the hospital to which the patient was admitted, their main diagnosis, the date of admission and the date of discharge) at each scheduled clinical examination. Information on diagnosis-related groups (Groupe Homogène de Malades; inpatient setting) or management-related groups (Groupe Homogène de Prise en Charge; home care setting) will be requested at the end of the study by the study coordinator from hospitals to which patients were admitted. Nutritional products will be valued at their current price.

Quality-adjusted life years will be computed using the French value set by a linear interpolation between dates of measurement (inclusion and days 30, 60, 90 and 180) [29]. Considering follow-up, costs and quality-adjusted life years will not be discounted.

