## Methods/design

### Protocol overview

The NUTRILEAK trial is a multicenter, randomized, parallel-group, open-label, phase III study to assess the efficacy of EN compared to TPN in patients with PUGIF. After informed consent, patients will be randomized in a 2:1 ratio to the EN treatment arm and the TPN comparator arm. Patients will be randomized to receive EN through jejunostomy or nasojejunal tube, or to receive TPN through central venous access, a peripherally inserted central catheter line, totally implantable venous access or any other approved TPN device.

Any other surgical or endoscopic procedures aiming at directly closing the defect will not be allowed (including surgical closure and endoscopic clip, prosthesis or glue) throughout the whole study period. These measures have not been scientifically demonstrated to be efficient in this situation at this time and could be a confounding factor regarding our primary objective.

By contrast, surgical, radiological or endoscopic fistula drainage will be allowed throughout the whole study period. Any interruption of more than 24 h in the treatment determined by randomization (EN or TPN) will be reported, with the cause, duration and solutions given (i.e., the treatment provided or a switch to TPN in the EN group). During hospitalization, patients will be evaluated daily until fistula closure, with any fistula- or protocol treatment-related complication viewed through physical examination and, if required, through routine laboratory tests and/or imaging according to the usual practice of each center.

The present study protocol was written in compliance with the Standard Protocol Items: Recommendations for Interventional Trials (SPIRIT) 2013 [21]. A completed SPIRIT checklist is available as Additional file 1, and the schedule of this study is presented in Fig. 1.

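### The 90% power makes no allowance for the TPN-to-EN switching that the protocol itself expects, and the direction of switching differs between sections

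*Protocol article*

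**What the plan says.** **Expected switching.** In the protocol article, Medico-economic analysis, the complementary per-protocol economic analysis is justified by the statement that "many patients are expected to switch from TPN to EN". No rate and no time window are attached.

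**Switching described elsewhere.** The Protocol overview asks for every treatment interruption of more than 24 h to be reported in either arm. Its examples of the solution given are "the treatment provided or a switch to TPN in the EN group". The worked example under Statistical evaluation and sample size is also an EN patient who moves to TPN. That patient stays in the EN group for ITT and is counted with TPN in the per-protocol analysis.

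**Sample size.** The same section states that "the 30-day fistula closure rate is expected to be 35% in the TPN group and 55% in the EN group" and describes this as an "absolute difference of 20%, relative risk 1.57". The other inputs are "a two-sided test, a type I error of 0.05, a 90% power" and "an allocation rate of 2:1 for the EN group and the TPN group". The only adjustment is for 10% mortality at 30 days, which leads to 214 EN and 107 TPN patients, 321 in total.

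**Analysis population.** The primary outcome is analysed by ITT, regardless of the treatment received. A per-protocol analysis of the primary outcome is secondary.

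**The concern.** ITT keeps switchers in the arm to which they were randomised. A TPN patient who moves to EN before closure and within 30 days tends to raise the TPN closure rate if EN works. An EN patient who moves to TPN tends to lower the EN rate. Both shrink the difference that the primary test is meant to detect.

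One section expects a good deal of such switching. Another computes power as though the full 20-point difference survives into the ITT comparison, and does not say why it should. If an appreciable share of patients switch early, an EN strategy that truly works has a lower chance of a significant primary result than the stated 90%. The sponsor and readers would not know this from the protocol.

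The sections also do not agree on the direction of switching. It is therefore unclear which arm's rate is expected to move.

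**Working it through.** **Inputs** (Statistical evaluation and sample size): p_TPN = 0.35, p_EN = 0.55, two-sided α = 0.05 (z = 1.960), power 90% (z = 1.2816), allocation 2:1, mortality 10%.

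**Step 1: reproduce the plan's figure.** Pooled-variance formula for two proportions, no continuity correction, n the TPN arm and 2n the EN arm:

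n = [1.960·√(1.5·p̄(1−p̄)) + 1.2816·√(p_TPN(1−p_TPN) + p_EN(1−p_EN)/2)]² / (p_EN − p_TPN)²

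with p̄ = (0.35 + 2×0.55)/3 = 0.4833. This gives n = 95.95, so 96 TPN and 192 EN, 288 evaluable. Then 96/0.9 = 106.7, rounded up to 107, and 2 × 107 = 214. The total is 321, an exact match. The whole step from 288 to 321 is used for mortality.

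**Step 2: power with no switching.** Power = Φ[(p_EN − p_TPN − 1.960·SE₀)/SE₁], where SE₀ is the pooled and SE₁ the unpooled standard error. At 96/192, SE₀ = 0.06247 and SE₁ = 0.06049, so (0.20 − 0.12243)/0.06049 = 1.282 and power is 90.0%.

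**Step 3: add switching.** The documents give no rate, so the share s is an assumption. It counts only patients who switch before closure and within 30 days. If they take the other arm's full closure rate:

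- TPN to EN: p_TPN = 0.35 + 0.20·s, p_EN = 0.55
- EN to TPN: p_TPN = 0.35, p_EN = 0.55 − 0.20·s

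If TPN-to-EN switchers gain only half the effect, p_TPN = 0.35 + 0.10·s.

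| s | TPN to EN, full effect | EN to TPN, full effect | TPN to EN, half effect |
|---|---|---|---|
| 0% | 90.0% | 90.0% | 90.0% |
| 5% | 86.7% | 86.8% | 88.4% |
| 10% | 82.7% | 83.0% | 86.7% |
| 20% | 72.9% | 73.5% | 82.7% |
| 30% | 61.2% | 61.9% | 78.1% |

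Example at s = 20%: p_TPN = 0.39, difference 0.16, SE₀ = 0.06250, SE₁ = 0.06138; (0.16 − 0.12249)/0.06138 = 0.611, power 72.9%. With full effect, power reaches 80% at about 13% switching. With 10% switching in each direction (0.37 vs 0.53) it is 73.1%.

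**Step 4: sensitivity to who is counted and to the planning rates.**

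- All 321 counted at 35% vs 55%: 92.9% with no switching and 90.1% at 5% full-effect TPN-to-EN switching.
- All 321 counted with deaths as non-closures (0.9 × 35% = 31.5%, 0.9 × 55% = 49.5%): 87.5% before any switching.
- True rates equal to the 37% vs 60% cited in the Background, at 96/192: 96.2% with no switching, 91.7% at 10% and 84.3% at 20%. About 12% still leaves 90%.

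**The case against.** **The planning rates may already allow for switching.** They are attributed to a randomised trial and lie below the 37% and 60% quoted from it. This may be right, but the protocol neither gives a reason for the lower rates nor says whether the source rates include switching. It is a reason to ask for one sentence, not a reason to assume an allowance.

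**The sentence on switching may not concern the first 30 days.** It stands in an economic analysis that uses measurements to day 180. Only switches before closure and within 30 days affect the primary endpoint. This stands, and it is why no single power figure can be put on the expected switching.

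**The full-effect figures are pessimistic.** They treat each switcher as if on the other treatment from the start. Later switchers would take only part of the effect. This also stands, hence the half-effect column.

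Four stronger readings are tempting, and the document does not support them:

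- A reader might infer that 90% power holds only if nobody switches. That is so at 288 evaluable patients and exactly 35% vs 55%. If all 321 count at those rates, about 5% switching is tolerated.
- A reader might take "it will be necessary to start a complementary parenteral nutrition to make up the nutritional requirements" (Treatment methods) as a further switch. It describes supplementing continuing EN, not leaving it.
- A reader might conclude that either the expected direction or the treatment rules must be misstated, because no TPN-to-EN switch is provided for. That does not follow. Interruptions are to be reported in both arms, and in an open-label trial departures can be expected without being permitted.
- A reader might say that a null result could not be interpreted. It would still estimate the effect of assignment, and a secondary per-protocol analysis is prespecified. That analysis does not restore the power of the primary comparison.

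**Conclusion.** The concern holds as an inconsistency between the expected switching and the stated power. The figure of 321 is computed correctly from its inputs, and all of its inflation goes to mortality. Nothing in the stated derivation covers the switching expected in the Medico-economic analysis section.

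On the 96/192 basis, the loss is about 3 points at 5% switching, 7 at 10%, 17 at 20% and 29 at 30%. This assumes that switches occur before closure and within 30 days and carry the other arm's full closure rate. With half the effect, the loss at 20% is about 7 points. Either direction gives nearly the same values, so a simple reversal of direction in the economic section would not by itself remove the problem. The switch rates are assumptions, and the true loss could be small if most switches come late or if 35% and 55% already include them.

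The disagreement on direction does not depend on these assumptions: the economic section expects TPN to EN, while the examples in the other two sections run from EN to TPN.

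**What to change.** 1. Keep 321 patients and the ITT primary analysis.
2. In Statistical evaluation and sample size, state the expected share switching within 30 days in each direction, and restate the power of the ITT comparison as a range over plausible rates. Alternatively, state that 35% and 55% are ITT rates that already include switching, and explain why they lie below the cited 37% and 60%.
3. Reconcile the direction of switching in the Medico-economic analysis with the Protocol overview and the worked example in the sample size section. Which direction is correct is for the sponsor to say.
4. Report the proportion switching by day 30, by arm, beside the primary result.

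The cost is a few sentences and probably a less favourable stated power. Interruptions of more than 24 h are already to be reported with cause, duration and solution in both arms, so the reporting in item 4 should need little or no new data.

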### End points

The primary end point is the fistula closure rate at 30 days after randomization. Fistula closure will be defined as no output fluid for 48 h in the wound or drainage and absence of any fluid collection on imaging (CT scan with contrast injection). The secondary end points are: 1) 6-month fistula closure rate; 2) time of first fistula closure, defined as time in days from randomization to first fistula closure within 6 months after randomization; 3) medical and surgical treatment-related complication rate at 6 months, including complications related to the nutritional support such as tube -related complications (dislodgment, infection, occlusion), venous catheter -related complications (thrombosis, infection), or any other nutritional route-related complications; 4) fistula-related complication rate at 6 months; 5) type and severity of early (before 30 days after randomization) and late (over 30 days after randomization) complications according to the Dindo–Clavien classification [22]; 6) mortality within 30 days and within 6 months after randomization; 7) nutritional status will be evaluated at day 30, day 60, day 90 and day 180 postrandomization based on weight, serum albumin and prealbumin concentration, C-reactive protein and grip test (muscular strength); 8) length of hospital stay in a health care structure (including home hospitalization) based on the cumulative number of days of hospitalization during the whole study period (from randomization until the end of the study); 9) patient health-related quality of life score based on the 36-item Short Form and EuroQoL five-dimensions questionnaires at inclusion and at days 30, 60, 90 and 180; 10) time from randomization to the oral diet covering at least 60% of the patient’s daily requirement ; 11) direct economic costs of therapy from a societal perspective, including the costs of hospitalization (inpatient and home settings), nutritional products, and early and late complications occurring during follow-up.

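### The inpatient cost is adjusted to a length-of-stay end point that also counts home-hospitalization days, while home hospitalization is costed separately; followed as written, home days enter both costings

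*Protocol article*

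**What the plan says.** The point rests on two sections of the Protocol article.

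- **End points, item 8** defines the trial's only length-of-stay end point: "length of hospital stay in a health care structure (including home hospitalization) based on the cumulative number of days of hospitalization". The count runs from randomization to the end of the study, which is six months for each patient.
- **Medico-economic analysis** lists "hospitalization (inpatient and home settings" settings together as one cost component, then costs the two settings from different sources. For the first: "The costs of hospitalization (inpatient) will be computed using the French hospital production costs study". The rule for adjusting that cost follows at once: "The average cost will be adjusted to the length of stay (secondary end point) and the number of days in intensive care units". The next sentence turns to the second setting: "Home hospitalizations will be valued by reference to the French home hospitalization production costs study".

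The economic section also describes data that keep stays and settings apart. Each hospitalization is recorded with the hospital, "their main diagnosis, the date of admission and the date of discharge", and the groupings requested at the end of the study differ by setting: "Information on diagnosis-related groups (Groupe Homogène de Malades; inpatient setting) or management-related groups (Groupe Homogène de Prise en Charge; home care setting").

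**The concern.** The parenthesis in the adjustment rule points to a specific end point, and that end point contains home days. An analyst who follows the reference puts home days into the inpatient adjustment and then values the same days from the home-care source. Nothing in the article removes them from the first step.

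There is a second mismatch. The end point is one total per patient over all stays in six months, whereas the average cost being adjusted belongs to an inpatient stay. This remains even for a patient with no home days who is readmitted.

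The economic section itself treats length of stay and intensive-care days as what chiefly determines cost. An error here therefore falls on a large component of the direct-cost end point and on the numerator of the cost-effectiveness ratio. Home days could plausibly differ between arms. Artificial nutrition continues until oral intake is sufficient, oral feeding resumes only some days after closure, and the plan expects closure to differ: "Considering a 35% fistula closure rate in the TPN group and an expected 55% rate in the EN group". The article does not say in which direction home days would differ.

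**Working it through.** **The plan's own figure.** The article gives no cost per day, expected stay or expected number of home days, so there is no economic figure to reproduce. The one design figure that can be recomputed is the sample size. With 35% versus 55%, two-sided 0.05, 90% power, 2:1 allocation and no continuity correction, 96 TPN and 192 EN patients are needed. Dividing by 0.9 gives 106.7 and 213.3, rounded up to 107 and 214, total 321 as stated. The present point does not depend on it.

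**Notation.** Let *a* be the inpatient cost per day, *h* the home cost per day and *r = h/a*. Let *I* and *H* be a patient's inpatient and home days, and *dI* and *dH* the EN-minus-TPN differences in their means. I assume the adjustment is linear in days; the article does not define it. Intensive-care days are left out because they are the same under both readings.

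**Cost per patient**
- Settings kept apart: *aI + hH*
- Text as written: *a(I + H) + hH*
- Excess: *aH*

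**Incremental cost, EN minus TPN**
- Settings kept apart: *a·dI + h·dH*
- Text as written: *a(dI + dH) + h·dH*
- Error: *a·dH*, which is zero when mean home days are equal

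**When the sign reverses.** Suppose EN saves *x* inpatient days, so *dI = −x*. EN is cheaper with settings kept apart if *−x + r·dH < 0*, that is *dH < x/r*. It looks dearer under the text as written if *−x + (1 + r)·dH > 0*, that is *dH > x/(1 + r)*. Reversal therefore needs *x/(1 + r) < dH < x/r*. For *x* = 5:

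| Assumed *r* | Lower limit, 5/(1+*r*) | Upper limit, 5/*r* |
|---|---|---|
| 0.1 | 4.55 | 50 |
| 0.2 | 4.17 | 25 |
| 0.3 | 3.85 | 16.67 |
| 0.5 | 3.33 | 10 |

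**Illustrations.** Assumed *a* = 1000 and *h* = 200 (so *r* = 0.2), with assumed day counts:

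| EN days (inpatient + home) | TPN days (inpatient + home) | *dH* | Difference, settings apart | Difference, as written | Effect |
|---|---|---|---|---|---|
| 30 + 10 | 35 + 10 | 0 | −5000 | −5000 | none |
| 30 + 14 | 35 + 10 | +4 | −4200 | −200 | shrunk, same sign |
| 30 + 20 | 35 + 10 | +10 | −3000 | +7000 | reversed |
| 30 + 10 | 35 + 20 | −10 | −7000 | −17000 | exaggerated, same sign |

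The third row in full: with settings apart, EN costs 30 × 1000 + 20 × 200 = 34000 and TPN 35 × 1000 + 10 × 200 = 37000. As written, EN costs 50 × 1000 + 20 × 200 = 54000 and TPN 45 × 1000 + 10 × 200 = 47000.

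**Six-month total applied to a stay.** If a patient has *k* inpatient stays totalling *L* days and the total *L* is used to adjust each stay, the adjustment rests on *kL* days instead of *L*. It is right only when *k* = 1 and there are no home days.

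**The case against.** The strongest defence is that the economic section reads as costing by stay and by setting. The sentence before the adjustment rule confines it to inpatient care, the sentence after gives home care its own source, each hospitalization has its own dates, and the groupings are separate. The reference to the end point may only signal that length of stay is also a trial outcome. A six-month total fits the average cost of a stay so poorly that literal application may not be what was meant.

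Much of this stands. It shows that a correct costing is feasible and perhaps intended. It does not show that the plan specifies one. To reach it, the analyst must set aside the end point the rule names, and the statistical section requires departures from the specified analysis to be documented.

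Nor is this detail that a condensed article may leave to the full protocol: the article states a rule and names the wrong quantity in it.

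A reader might infer more: that home days will certainly be charged twice, or that the cost comparison will come out with the wrong sign. The documents support neither. Double charging follows from the wording, not from any analysis shown. Reversal needs the arms to differ in opposite directions on inpatient and home days, within the limits shown in the working. The documents contain no unit costs or day counts that would place the trial inside or outside those limits.

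**Conclusion.** The cross-reference is wrong as written. It makes a cumulative total that contains home days the adjuster of an inpatient cost, although home care is costed on its own.

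Under a linear adjustment the error in the incremental cost is the inpatient cost per day multiplied by the between-arm difference in mean home days. Depending on that difference, the comparison may be untouched, shrunk, exaggerated or, in a restricted range, reversed. Even when the difference is untouched, each arm's total is too high if there are any home days. Every monetary and day figure used here is an assumption, as is linearity.

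Only the secondary economic end point and the cost-effectiveness analysis built on it are affected; the primary end point and the sample size of 321 are not. The sentence should be corrected before the economic analysis is run.

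**What to change.** In Medico-economic analysis, replace the reference to the length-of-stay secondary end point with *inpatient length of each stay, excluding home hospitalization*, and keep intensive-care days as the other adjuster. Add that home-hospitalization days are used only in the home-care costing.

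The cost is one sentence in the protocol or the analysis plan. Little or no new data collection appears necessary, since admission and discharge dates are recorded for every hospitalization and the inpatient and home-care groupings are to be requested separately.

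Item 8 of the end points can stay as defined. Reporting it split into inpatient and home days would help readers follow the costing, but is optional.
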